### **3.6.6 Subject Follow-up and Contact**

All subjects who are assigned a subject identification number and receive study vaccine will be followed according to the protocol unless consent is withdrawn.

Subjects will be instructed to contact a study team member to report new diagnoses or new or worsening adverse events and to come to the study clinic if medical attention is needed, provided the urgency of the situation permits. For emergencies and other unscheduled visits to a medical facility other than the study clinic, medical records will, to the extent possible, be obtained by the investigator.

During each clinic visit, subjects will be reminded to notify a study team member of the following:

- The occurrence of AEs and SAEs during the respective reporting periods
- Receipt of any concomitant medications during the applicable reporting period
- Plans to move or if contact information changes
- If subject has decided to withdraw from the study
- Change in general health status
- Any other change in status that may affect the subject's participation (e.g., plan to participate in another investigational study)

All deviations from protocol procedures, evaluations, and/or visits must be categorized and documented as they occur. Each deviation must be documented on a Protocol Deviation Form. A cumulative record of all protocol deviations must be maintained on a Protocol Deviation Log. When possible, missed visits and procedures must be rescheduled and performed at the nearest possible time point to the original schedule.

Protocol deviations are to be categorized as follows:

1. Informed consent was not properly obtained.
2. A subject did not meet inclusion/exclusion criteria but was entered into the study.
3. A subject developed withdrawal criteria during the study but was not withdrawn.
4. There was a deviation in randomization, vaccine preparation, or dosing.
5. A protocol-specified visit or procedure was performed out of the allowable window.
6. A protocol-specified visit or procedure was missed (not performed).
7. Other (to be specified in the appropriate documentation)

The signature of the Principal Investigator is required on the Protocol Deviation Form for categories 2 through 5. Certain protocol deviations may also meet the criteria for an Immediately Reportable Event as described in Section 5.12.

### 3.6.7 Loss to Follow-up

If the site's study team members are unable to establish contact with a subject who misses a scheduled study visit, the clinical site must make every possible effort to re-establish contact with the subject and document such efforts. If contact is re-established, then the subject will resume participation in the study.

If contact with the subject cannot be re-established by the subject's expected End-of-Study visit date, then a determination of "lost to follow-up" can be made.

## 4 STUDY VACCINES

Staff at the clinical research site will refer to the most current version of the Study Vaccine Management Manual (provided under separate cover) for further instructions on vaccine/placebo storage and preparation. Additional information is also provided in the Investigator's Brochure.

### 4.1 Supplies

Aeras will provide the study vaccine manager with adequate quantities of MVA85A/AERAS-485 and Candin (placebo) for the study prior to the start of vaccination.

**MVA85A/AERAS-485** is manufactured in accordance with GMP by Impfstoffwerk Dessau-Tornau (IDT) Biologika GmbH, [name]. A description of the contents of the vials follows.

MVA85A/AERAS-485: formulated in Tris buffer (10 mM Tris, 140 mM NaCl, pH 7.7) at a target concentration of between  $4 \times 10^8$  and  $1 \times 10^9$  plaque-forming units (pfu)/mL. The dose of study vaccine to be administered will be  $1 \times 10^8$  pfu.

**Candin®** is manufactured by Allermid Laboratories, Inc., San Diego, CA, USA and is licensed for the evaluation of delayed-type hypersensitivity reactions in adults.

Candin is produced from a culture filtrate of two strains of *Candida albicans* grown on a defined medium of inorganic salts, biotin, and sucrose. Lyophilized source material is extracted with a solution of 0.25% NaCl, 0.125% NaHCO3, and 50% w/v glycerol. The concentrated extract is diluted with a solution of 0.5% NaCl, 0.25% NaHCO3, 0.3% human albumin USP, 8 ppm polysorbate 80 and 0.4% phenol.

Candin is supplied as a clear, colorless solution. Candin is usually administered intradermally at a dose of 0.1 mL, but for this study it will be administered at a dose volume to match the volume of the MVA85A/AERAS-485 dose.

### 4.2 Accountability

The study vaccine manager is required to maintain accurate study vaccine accountability records. Instructions and required forms to be completed and kept for accountability will be provided to

the study vaccine manager. Upon completion of the study, all study vaccine management records will be copied and the copies returned to Aeras or its designee. The originals must be maintained at the clinical site with the rest of the study records.

### **4.3 Receipt and Storage**

Upon receipt of study vaccine supplies, the study vaccine manager must immediately inspect all vials for damage. Study vaccine/placebo will be shipped with a continuous temperature-monitoring device. The temperature of the shipment must be documented by the study vaccine manager. Any deviations or problems identified must be documented and promptly discussed with Aeras and the study monitor to determine the usability of the supplies or if replacements must be sent.

Study vaccine/placebo must be stored in a secured location with no access for unauthorized personnel. Study vaccine/placebo should be placed in a container clearly marked "For Clinical Trial Use Only".

**MVA85A/AERAS-485** will be stored frozen at -40° C or colder in a frost-free or frostless freezer. Vaccine potency is not affected by long-term storage at temperatures up to -20°C, but viral titers may be affected and, therefore, the vaccine should not be kept at -20°C for more than 72 hours. Storage temperature must be monitored continuously and a log of the monitored temperature maintained. The freezer must be equipped with a continuous temperature monitor (wheel device) or should be alarmed in case the temperature exceeds specified ranges. Complete storage instructions will be provided in the Study Vaccine Management Manual.

**Candin** must be stored refrigerated at 2°C to 8°C (36°F to 46°F) and must not be frozen. Storage temperature should be monitored daily, and a log of the monitored temperatures must be maintained.

### **4.4 Vaccine/Placebo Preparation**

Preparation of the study vaccine/placebo for injections should not begin before a subject is confirmed eligible on Study Day 0 or Study Day 168-196 for the booster vaccination. Subjects must also be in the clinic on these days and must agree to receive the vaccine/placebo on the same day.

The study vaccine manager will follow the detailed instructions provided in the Study Vaccine Management Manual to prepare the doses of study vaccine/placebo using aseptic technique. One vaccine vial per subject to be immunized will be used. The study vaccine will be allowed to thaw to room temperature before being withdrawn into a masked syringe and administered within 2 hours. The study vaccine manager will draw the appropriate volume of study vaccine/placebo into the masked syringe, will label the syringe with the subject's identification number and initials, the date and time of preparation, and the volume in the syringe.

To prepare an injection of Candin, sanitize the vial cap with 70% alcohol on a sterile cotton pad. Using a 1 mL Tuberculin syringe with a short 25- to 26-gauge needle, withdraw the appropriate

volume of Candin. Each vial of Candin may be used to prepare injections for more than one subject.

Precautions should be taken to avoid contact of the study vaccine/placebo with broken skin, and gloves and eye protection (safety goggles) should be worn.

Preparation of the vaccine/placebo including date and time must be documented in the study vaccine management records by the study vaccine manager who prepared the doses.

#### **4.5 Disposal of Unused Supplies**

All unused study vaccine and supplies will be returned to Aeras at the end of the study or disposed of upon authorization from Aeras or according to the facility's SOPs. Any disposing of study vaccine conducted at the clinical site will be documented in the study file.

### **5 SAFETY**

#### **5.1 Responsibilities for Ensuring the Safety of Trial Subjects**

The national regulatory authority, the vaccine sponsor (Aeras), the institution through which the research is performed and all members of the principal investigator's clinical team share responsibility for ensuring that participants in this trial are exposed to the least possible risk of adverse events that may result from participation in this protocol.

##### **5.1.1 Principal Investigator**

The principal investigator has a personal responsibility to closely monitor trial subjects and an inherent authority to take whatever measures necessary to ensure their safety. The principal investigator has the authority to terminate, suspend or require changes to a clinical trial for safety concerns and may delay an individual's study vaccine administration or pause study vaccine administration in the whole trial if the investigator has some suspicion that the study vaccine might place a subject at significant risk. The principal investigator determines severity and causality with respect to the study vaccine for each adverse event. For blinded studies the principal investigator is blinded, in which case the study vaccine may consist of a placebo, an active control, or the investigational product.

##### **5.1.1.1 Pausing Rules for the Principal Investigator**

If the principal investigator determines that a SUSAR OR a serious adverse event OR an adverse event pattern of concern that is judged to be POSSIBLY, PROBABLY or DEFINITELY related to study vaccine has occurred, the principal investigator will pause administration of study vaccine in the trial. If the principal investigator pauses study vaccine administration he or she will record this in a memorandum to the study file and notify the sponsor.

If the principal investigator pauses study vaccine administration in a trial under the rules in this section and additional clinical information becomes available that reduces the principal

investigator's assessment of causality, severity or toxicity grade and no longer requires pausing then the principal investigator, with the agreement of the local medical monitor, may resume study vaccine administration with a memorandum to the study file and notification of the sponsor.

### **5.1.2 Study Sponsor**

The sponsor (Aeras) also has an institutional responsibility to ensure subject safety. This responsibility is vested in two medical monitors (one local medical monitor and one global medical monitor) and a data monitoring committee (DMC).

### **5.1.3 Local Medical Monitor**

The local medical monitor is the sponsor's representative and is a credentialed physician or surgeon in their country of residence (or geographical region) with the necessary expertise to act in such capacity. The local medical monitor reviews the safety of the product for protocols in a specific region and determines the expectedness. The local medical monitor may make a sponsor's assessment of severity and causality for adverse events that may upgrade the degree of severity and causality determined by the principal investigator. The local medical monitor, like the principal investigator, is blinded for a blinded study.

#### **5.1.3.1 Pausing Rules for the Local Medical Monitor**

If the local medical monitor determines that a SUSAR OR a serious adverse event OR an adverse event pattern of concern that is judged to be POSSIBLY, PROBABLY or DEFINITELY related to study vaccine has occurred, the local medical monitor will pause administration of study vaccine in the trial. If the local medical monitor independently pauses the administration of study vaccine in the study, he or she will record this in a memorandum to the study file and notify the principal investigator and sponsor who will then convene the DMC. In all cases administration of study vaccine may resume only if permitted by the DMC. Any changes to the protocol required by the DMC as a condition of study vaccine resumption must be approved by, or submitted to, the Institutional Review Board/Ethics Committee and the national regulatory authority.

### **5.1.4 Global Medical Monitor**

The purpose of the Global Medical Monitor (GMM) is to authorize SUSAR (Suspected Unexpected Serious Adverse Reaction) reporting to regulatory agencies without unblinding the sponsor, protocol team or the clinical research sites. Aeras retains a GMM through the contract research organization PPD, Inc., located in Cambridge, UK. The GMM reviews and unblinds all SUSAR reports and, if he or she deems it necessary, may review and unblind selected SAE reports. The GMM may contact the clinical research sites directly if additional information is needed for assessment of the SUSAR. For all SUSARS the GMM will make available to the sponsor and the clinical research sites a completed blinded CIOMS II so that the sites and sponsor may remain blinded.

### **5.1.5 Data Monitoring Committee**

If study vaccine administration is paused by the principal investigator, the local medical monitor, or the global medical monitor, a Data Monitoring Committee (DMC) will be convened. The composition of the DMC will be described in the DMC charter but will include at least two voting physicians with experience in evaluation of investigational product safety issues and a voting statistician. The voting members cannot be directly involved with the conduct of the study. Voting members cannot be employees of Aeras. Additional subject area experts may be present to provide expertise if requested by the DMC. The DMC may review an individual SAE or it may choose to review adverse events, serious adverse events, solicited adverse events, and laboratory and vital signs data. The DMC may unblind any amount of safety information needed to conduct their assessment. All procedures associated with this review, including objectives, data handling, and elements to be included for review will be documented in the DMC minutes.

After the 200th subject enrolled has completed one month of follow-up post-primary vaccination, a DMC will evaluate blinded and unblinded-by-group safety data (including CD4 counts) to determine if a pattern of adverse events related to MVA85A/AERAS-485 or other safety or risk concerns exist. The DMC will conduct a second unblinded-by-group safety and risk review after the 600th subject enrolled has completed one month of follow-up post-primary vaccination. If a safety risk exists, the DMC will determine if changes to the study protocol need to be made for subjects' safety. Only the DMC and the independent statistician responsible for preparing these analyses would be unblinded during these reviews.

Based on its review and the protocol stopping rules (Section 6) the DMC will make recommendations in the DMC minutes to Aeras regarding further conduct of the study and further administration of study vaccine. The conclusions of the DMC will be communicated to the investigators and the Institutional Review Boards/Ethics Committees and the national regulatory authority for their concurrence. The sponsor agrees to abide by the decision of its DMC with concurrence of the national regulatory authority, the Institutional Review Board or Ethics Committee and the principal investigator.

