## **6 STOPPING RULES**

These rules govern the stopping of study vaccine administration at any time during the study. Stopping rules will include:

- Death in any subject that the DMC determines is RELATED to MVA85A/AERAS-485
- An anaphylactic reaction to MVA85A/AERAS-485 in any subject
- A life-threatening adverse event in any subject that the DMC determines is RELATED to MVA85A/AERAS-485
- A serious adverse event that the DMC determines is RELATED to MVA85A/AERAS-485
- A pattern of significant symptoms, physical findings or laboratory abnormalities (adverse events) that, although individually minor, collectively represent a safety concern in the opinion of the investigator or the medical monitor and that the DMC determines are RELATED to MVA85A/AERAS-485

The DMC may permit resumption of study vaccine administration if the study pause was for reasons less severe than those in the DMC stopping rules. The DMC may permit resumption of enrollment if it judges that changes to the study protocol will eliminate or greatly reduce the safety risks specified in the stopping rules. In the absence of study protocol changes the DMC must follow the DMC study stopping rules.

If a decision to resume study enrollment and study vaccine administration is made the DMC will record their judgment in a memorandum to the study file and notify the sponsor, who will then forward the DMC memorandum to the medical monitors and principal investigators. The clinical site will be allowed to resume activities upon receipt of written notification from the sponsor. The appropriate regulatory authority will be informed in writing if the study is stopped and will be informed in writing of the decision by the DMC to resume or discontinue study activities.

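### At the two planned unblinded reviews, a non-serious pattern visible only by arm does not by itself meet the Section 6 stopping rules, and Section 5.1.5 then ties a DMC stop to outside concurrence without requiring a dosing hold

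*Protocol*

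**What the plan says.** **Protocol Section 5.1.5** plans two safety reviews unblinded by group, one month after the 200th and the 600th subjects receive their first dose. CD4 counts are named among the safety data. The aim is "to determine if a pattern of adverse events related to MVA85A/AERAS-485 or other safety or risk concerns exist". On access: "Only the DMC and the independent statistician responsible for preparing these analyses would be unblinded during these reviews". The DMC makes recommendations to the sponsor, drawing on its review and on Section 6. Its conclusions go to the investigators, ethics committees and regulator for concurrence, and the sponsor's commitment reads: "abide by the decision of its DMC with concurrence of the national regulatory authority, the Institutional Review Board or Ethics Committee and the principal investigator". Stopping is not treated differently from continuing or resuming.

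**Protocol Section 6** opens: "These rules govern the stopping of study vaccine administration at any time during the study". It lists related deaths, related life-threatening events, related serious events and anaphylaxis. Its last rule covers individually minor findings that "collectively represent a safety concern in the opinion of the investigator or the medical monitor and that the DMC determines are RELATED" to the vaccine. On the regulator's role it says: "The appropriate regulatory authority will be informed in writing if the study is stopped".

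**Blinding.** Section 5.1.3: "The local medical monitor, like the principal investigator, is blinded for a blinded study". Under Section 5.1.4 the global medical monitor unblinds SUSAR reports and, where it is thought necessary, "may review and unblind selected SAE reports".

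**The concern.** The pattern rule has two conditions: a concern held by the investigator or a medical monitor, and a DMC finding of relatedness. At a planned review the evidence may exist only in the by-arm tables, which the holders of the first condition do not see. The DMC could be convinced of a related pattern and still not have a Section 6 trigger. Its recommendation would then fall back on Section 5.1.5, where the sponsor's commitment depends on the agreement of three outside parties, one of them the blinded principal investigator.

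Safety is the primary objective, and these are the two scheduled looks at data by arm. At stake is whether vaccination must be held between a DMC recommendation to stop and the replies from those asked to concur.

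**Working it through.** The plan gives no figure on this point, so the check is mainly textual.

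**Step 1. Which stops are already covered by Section 6?** The DMC alone can determine relatedness for a death, a life-threatening event or a serious event. Anaphylaxis is a rule in itself. What remains is a pattern of non-serious events or laboratory changes, such as a CD4 shift.

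**Step 2. Can the pattern rule be met from by-arm data alone?**

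| Whose opinion counts | Access to by-arm data at the planned reviews |
|---|---|
| Investigator (Section 5.1.1) | None; blinded |
| Local medical monitor (Section 5.1.3) | None; blinded |
| Global medical monitor (Section 5.1.4) | None; unblinds SUSARs and selected serious event reports only |
| DMC (Section 5.1.5) | Full, but its opinion does not satisfy the first condition |

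With 1:1 allocation, a mean shift of size d confined to one arm appears as (d + 0)/2 = d/2 in pooled data, so blinded observers see a diluted signal. The rule is not met until one of them adopts the concern.

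**Step 3. Is dosing already held?** In a review triggered by a pause, it is, and Section 5.1.3.1 lets it resume only with the DMC's permission. At a planned review no pause need be in force. Section 5.1.5 names the investigator and the two monitors, not the DMC, as those who pause. The action it states for a risk found at a planned review is to consider protocol changes.

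**Step 4. What other routes to a hold exist?**

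| Route | Effect | Depends on |
|---|---|---|
| Sections 5.1.1.1 and 5.1.3.1 | Pause is compulsory once a pattern of concern is judged at least possibly related | Investigator or local medical monitor making that judgement |
| Sections 5.1.1, 5.1.6, 5.1.7 | May suspend | Investigator, ethics committee or regulator |
| Sponsor | Not barred from stopping | Sponsor |
| Section 9.2 | No prior ethics approval needed for changes that remove immediate hazards | Someone deciding on the change |

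None takes effect on the DMC's recommendation alone.

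**Step 5. Illustrative size.** Inputs: 650 subjects and 21 months' enrolment (Section 7.6), boosters at day 168 to 252 (Table 2-1). Assumptions: even accrual, every subject boosted, the DMC meeting at its milestone, 30.44 days per month and 4.345 weeks per month.

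- Accrual: 650/21 = 30.95 per month; 30.95/4.345 = 7.1 per week.
- First doses and boosters together: 2 × 7.1 = 14.2 per week.
- Review 1: 200/30.95 + 1 = month 7.5. Boosters started at month 168/30.44 = 5.5 if given early, or start at month 252/30.44 = 8.3 if given late. Rate: about 14 per week with early boosters, about 7 with late ones until month 8.3.
- Review 2: 600/30.95 + 1 = month 20.4. About 631 are enrolled, so 19 first doses remain (19/7.1 = 2.7 weeks). Rate: about 14 per week until these are given, then about 7.

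With 1:1 allocation about half are active vaccine: roughly 3.6 to 7.1 per week.

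**The case against.** The strongest reply is that the message seeking concurrence is also the message that can trigger a hold. Section 5.1.5 sends the DMC's conclusions to the investigators. The pausing rules cover patterns as well as single events, set the threshold at possibly related, and are compulsory once the judgement is made. Nor does Section 6 say that the investigator's or monitor's opinion must come from by-arm data or precede the DMC's report. Either could adopt the concern and so meet the rule. Section 6 also does not present its list as exhaustive, and a DMC charter, not shown, may contain a hold.

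Much of this stands, and it rules out three stronger readings that a reader might infer:

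- *Section 5.1.5 delays every DMC stop.* It need not. Where a Section 6 rule is met, that section governs at any time.
- *All remaining safeguards are discretionary.* They are not. Sections 5.1.1.1 and 5.1.3.1 compel a pause once the judgement is made.
- *A known number of subjects would be dosed in the interval.* The documents give no concurrence time, and any informed party might act at once.

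What the reply does not remove is the dependence on a blinded party, or an outside body, accepting a conclusion whose by-arm evidence only the DMC and its statistician saw. The protocol cites the charter for the committee's composition, and a hold placed there would still sit beside the concurrence wording.

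**Conclusion.** The point holds in a limited form. For a non-serious adverse event or CD4 pattern seen only by arm at a planned review, Section 6 is not met by the DMC's finding alone. Section 5.1.5 then makes the sponsor's commitment conditional, with no exemption for a stop and no required hold. This is a gap in the rule, not a demonstrated delay. It matters only if such a pattern arises, the DMC recommends stopping, and no other party acts promptly.

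The figure of about 7 to 14 injections per week across both arms only illustrates scale. It rests on the assumptions in the working and on nobody acting in the interval; it does not measure expected harm.

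**What to change.** 1. In Section 6, let the pattern rule be met by the opinion of the investigator, the medical monitor or the DMC.
2. In Section 5.1.5, state that vaccination is held at once when the DMC recommends a stop or pause, that investigators, ethics committees and regulator are notified in parallel, and that concurrence applies only to resumption or protocol changes.

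The cost is one or two sentences and a few words, with no extra data, visits or staff. The downside is a possible short hold that is later lifted, with some boosters falling out of window. Tables 0-1 and 2-1 and Appendix A give day 168 to 252, a width of 252 − 168 = 84 days, so a 28-day hold would push out only subjects already in the last 28 days. Section 4.4 gives day 168 to 196, a width of 28 days, which such a hold would use up entirely. Section 4.4 should be brought into line at the same time.
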